## Abstract

**Background:**

Cardiovascular diseases are a leading cause of mortality worldwide. A significant contributing factor to this mortality is the lack of engagement in preventive activities. Consequently, strategies for enhancing adherence to and duration of physical activity (PA) have become pivotal. This project aims to create and validate innovative, disruptive, and secure technologies that ensure appropriate exercise intensity, bolster adherence to PA, and monitor health biomarker responses pre-, during, and post-physical activity.

**Methods:**

This exploratory study, followed by a noninferiority, investigator-blinded randomized clinical trial, will be divided into three phases: (1) development and validation of a sensor for real-time biofeedback during a functional assessment test; (2) integration of biofeedback and gamification into an app for the structured prescription of physical training within a controlled setting; and (3) implementation of biofeedback and gamification into an app for the prescription and monitoring of physical training in an uncontrolled setting. Phase 1 entails a validation test of a biosensor—monitoring heart rate (HR) and steps—during a modified shuttle walk test. In phase 2, the biosensor interfaces with a gamified smartphone application. The training regimen spans 6 weeks, 5 days weekly, with each session lasting 60 min: a five-min warm-up involving stationary gait, followed by 50 min of training at the target HR on the step and concluding with a five-min cool-down at a stationary pace. After 6 weeks of training, a new functional capacity test is conducted. Phase 3 involves an investigator-blinded, randomized clinical trial to demonstrate noninferiority. Participants are randomly assigned to either the intervention group (IG) or the control group (CG). IG participants practice exercise using the gamified application in an uncontrolled environment according to the prescribed method outlined in phase 2. CG participants receive PA practice guidelines exclusively.

**Discussion:**

Anticipated outcomes include improved exercise adherence through the gamified application, better maintenance of prescribed exercise intensity, and enhanced health biomarkers. The results of this study will inform health-related decision-making.

**Trial registration:**

The study protocol received approval from the Ethics Committee of Universidade Federal de Ciências da Saúde de Porto Alegre (54,492,221.80000.5345) and has been registered with the Brazilian Registry of Clinical Trials (ReBEC, RBR-359p69v).

## Administrative information

Note: The numbers in curly brackets in this protocol refer to SPIRIT checklist item numbers. The order of the items has been modified to group similar items (see)

## Introduction

### Background and rationale {6a}

Roughly 9% of premature deaths worldwide, equivalent to 5.3 million individuals, are directly attributed to physical inactivity [1]. Recently, the World Health Organization (WHO) estimates highlight that over 1.4 billion adults face the risk of developing or worsening conditions linked to inactivity [2]. However, since 2001, global levels of physical activity (PA) have stagnated. In 2016, more than a quarter (1.4 billion) of the global adult population was physically inactive, falling short of WHO’s aerobic exercise recommendations [3]. This sedentary lifestyle substantially heightens the risk of noncommunicable diseases and premature death [2]. The scientific community is intently focused on sedentary behaviour due to its detrimental link to health status, the rise of chronic noncommunicable diseases, and its prevalence across populations. Solid epidemiological evidence underscores the connection between sedentary behaviour duration and all-cause mortality rates [4].

According to WHO, up to 5 million deaths worldwide could be averted annually if people were more active and less sedentary. Moreover, engaging in physical exercises is pivotal for averting the onset and managing chronic noncommunicable diseases such as ischemic heart disease, stroke, chronic obstructive pulmonary disease, type 2 diabetes, and certain cancer types. In response, the WHO introduced a global action plan in 2018 aimed at reducing physical inactivity by 15% by 2030 [5]. Consequently, developing strategies to stimulate practice, participation, and adherence to physical activities within sedentary populations is imperative. The potential of gamified interventions is promising in promoting physical activity across diverse demographics [6]. These interventions leverage gaming techniques to infuse activities with playfulness, challenges, relevant rewards, and increased participant motivation, fostering lasting habits [7–9].

In this context, games offer a means to engage individuals in physical activity and educate them on cultivating regular exercise habits [10, 11]. For instance, games addressing healthy eating and exercise have been developed to combat childhood obesity [10]. Additionally, studies highlight the value of gaming in aiding respiratory rehabilitation [11].

Embracing new technologies, wearable sensors for tracking biological signals, and wireless sensor networks like low-power wide area network (LPWA) show promise in promoting physical exercise [12]. Their affordability, sustainability, and integration with the Internet of Things (IoT) make them accessible, especially when integrated into smartphones. Furthermore, they facilitate noninvasive biofeedback of physiological variables such as heart rate (HR) [13].

There are several brands of wearable devices that measure HR; however, they are expensive for the population [14, 15]. In addition to this technology, gamification has been the subject of attention and study as a way of encouraging physical exercise since 2010. A gap in the literature refers to the integration of gamification with wearable sensors that promote HR biofeedback [16].

### Objectives {7}

The primary goals of this study encompass three key objectives: (1) innovative technology development: the first objective revolves around the creation and validation of innovative and secure technologies—a biosensor and an app; these technologies are engineered to guarantee optimal intensity during prescribed physical exercises, setting the stage for a safe and effective workout experience; (2) enhanced adherence and monitoring: the second aim focuses on fostering heightened adherence to physical exercise routines while simultaneously monitoring health biomarker responses; these responses, encompassing heart rate and step data, will be tracked before, during, and after each session, providing valuable insights into the impact of the exercise regimen; and (3) sedentary lifestyle reduction: the third objective seeks to curb the prevalence of sedentary lifestyles within the population. By promoting engagement in physical activity through our technologies, we aim to contribute to a meaningful reduction in sedentary behaviours and their associated health risks.

### Trial design {8}

This study employs an exploratory design, succeeded by a noninferiority, investigator-blinded randomized clinical trial, to assess the viability of a gamified application prototype. The prototype incorporates a biofeedback system to guide physical exercises, ensuring adherence to prescribed intensity levels. The study protocol adheres to the guidelines set by Standard Protocol Items: Recommendations for Interventional Trial (SPIRIT) [17] and was registered in the Brazilian Registry Clinical Trials (ReBEC) by the identifier RBR-359p69v.

The study unfolds in three distinct phases: (1) validation of biosensor and app: this phase involves validating the functionality of the biosensor and app within the context of a functional assessment test; (2) validation of biofeedback and gamified application: the second phase encompasses the validation of the biofeedback and gamified application for prescribing and conducting physical training in a controlled environment; (3) validation of gamified application in noncontrolled setting: the final phase entails validating the gamified application for prescription and physical training within a noncontrolled environment. This validation will be executed through a noninferiority, investigator-blinded randomized clinical trial. The flowchart depicting the progression of trial participants can be found in Fig. 1.

**Fig. 1 Fig1:**
[figure not shown]
Flow Chart of participants. Asterisk (*) symbol indicates the following: from the 2875 individuals interviewed using the IPAQ, those identified as sedentary will undergo our eligibility screening. Subsequently, the qualified participants will be randomized

This study received approval from the Research Ethics Committee of UFCSPA prior to data collection, with registration number 54492221.80000.5345. The research team assumes responsibility for ensuring the integrity of this study.

## Methods: participants, interventions, and outcomes

### Study setting {9}

The sample will be conveniently recruited through a social media invitation in a city located in southern Brazil. This protocol was designed exclusively by researchers, without input from community members or patients.

### Eligibility criteria {10}

The recruitment of individuals will adhere to specific inclusion criteria: (i) individuals aged between 20 and 60 years without medical contraindication to engage in physical exercise, (ii) possession of a smartphone (cell phone with Android operating system), and (iii) willingness to participate in the research by signing the informed consent form. The exclusion criteria were experience angina during exertion, history of acute myocardial infarction within the 12 months prior to the start of the protocol, require oxygen supplementation, exhibit clinical instability in the month preceding the protocol initiation, uncontrolled hypertension, visual diseases that prevent the performance of the protocol, chronic conditions hindering participation in the exercise protocol, illiterate, and refuse to sign informed consent form.

### Who will take informed consent? {26a}

A proficient researcher will administer the informed consent form, ensuring that participants comprehend and willingly agree to participate in the study.

### Additional consent provisions for collection and use of participant data and biological specimens {26b}

On the consent form, participants will be asked if they agree to use of their data should they choose to withdraw from the trial. Participants will also be asked for permission for the research team to share relevant data with people from the universities taking part in the research or from regulatory authorities, where relevant. This trial does not involve collecting biological specimens for storage.

## Interventions

### Explanation for the choice of comparators {6b}

The World Health Organization recommends engaging in physical activity as a preventive measure against various diseases and for promoting overall health. This recommendation will be implemented within the control group.

## Intervention description {11a}

### Phase 1: Functional assessment and biosensor validation

Following the development of the wearable biosensor designed for heart rate and step count monitoring, a validation test will be conducted during the incremental shuttle walk test (ISWT) [18, 19]. This ISWT is a recognized, reliable, and secure walking test for assessing functional capacity. Throughout the evaluation, participants will wear the biosensor on their nondominant wrist to capture HR and step data. For HR measurement, the Polar H10 chest strap (Polar Electro Oy, Kempele, Finland) will serve as the reference [20], while the triaxial Actigraph GT3X accelerometer (Actigraph, Pensacola, Florida) will be used on the nondominant wrist to measure step count [21].

The assessment will encompass several variables, including maximum distance, top speed, oxygen consumption (VO_2_), tissue oxygenation, and blood pressure (measured at the test’s outset and conclusion). Continuous HR tracking will be achieved by both the biosensor under evaluation and the Polar H10 monitor. Additionally, perceived exertion will be recorded using the modified Borg scale [22]; other data to be captured include the stage and corresponding stage at which the test is stopped. Two ISWTs will be conducted, with a maximum interval of one week between them. The results from the most successful trial will be utilized for subsequent analyses. This phase will be executed within a research laboratory environment by trained researchers.

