### Outcomes {12}

Primary outcomes will encompass the following: (1) the concordance between HR and step count measurements assessed by the biosensor under test compared to standard devices (Polar H10 and ActiGraph, respectively); (2) participant perception regarding the utility of the gamified application for exercise engagement; (3) comparison with the prevalence of adherence to the physical activity protocol between the control and intervention groups; (4) evaluation of exercise capacity through ISWT, including stage and the corresponding phase at which the test was halted; and (5) measurement of oxygen consumption (VO_2_).

Secondary outcomes will include the following: (1) tissue oxygenation assessed via near-infrared spectroscopy (NIRS), (2) subjective perception of exertion during ISWT, (3) evaluation of endothelial function, and (4) assessment of autonomic function.

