### Sample size {14}

Since phases 1 and 2 consist of a pilot study for the clinical evaluation of a biosensor prototype and the gamified application that considers a biofeedback system for performing physical exercises, a convenience sample of 15 individuals without medical contraindications for PA will be studied. Assuming a sample loss of 30%, we will recruit 20 participants.

The third phase will be a noninferiority, investigator-blinded randomized clinical trial of the individuals eligible for the study—considering the same eligibility criteria as in phases 1 and 2, in addition to being sedentary—will be divided into two groups: the intervention group (IG), which will receive the exercise protocol through the biosensor and gamified application, and the control group (CG), which will only receive guidelines for performing PA. Considering a confidence level of 95%, power of 80%, ratio of 1:1 between the CG and IG, and estimated prevalence of adherence to the protocol of 70% and 50% for the IG and CG, respectively, it would be necessary to allocate 104 individuals in each group. Adding 30% for possible follow-up losses, 149 sedentary individuals will be assigned to each group, totalling 298 subjects in the study.

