For the progression of our study through its phases, we have set clear criteria to determine the acceptability of outcomes: *Phase 1*: We regard the study as satisfactory if the standard error between the biosensor under test and the reference measurements is within 5%. If this criterion is not met, we would reconsider moving to the next phase until the discrepancies are addressed. *Phase 2*: The study’s progression will depend on the functionality of the application. Should there be serious errors within the application that prevent exercise or significantly hinder adherence, we would need to address these issues before considering progression to phase 3. *Phase 3*: Here, our benchmark for continuation is achieving at least 70% adherence. Any value below this would prompt us to assess the reasons for the reduced adherence and potentially re-evaluate our approach. Additionally, it is important to note that throughout all phases, we have ensured that there are no operational issues related to the app. Thus, significant data recording failures in earlier phases would indeed influence our decision to proceed to the next phase.

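### The best-of-two rule for the ISWT is not limited to functional capacity, so as written it leaves one of two paired sensor sessions per participant out of the phase 1 agreement analysis

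*Protocol article*

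**What the plan says.** The section Phase 1: Functional assessment and biosensor validation makes the ISWT the setting in which the biosensor is validated. On the number of tests it says "Two ISWTs will be conducted, with a maximum interval of one week between them". On recording it says "Continuous HR tracking will be achieved by both the biosensor under evaluation and the Polar H10 monitor"; steps are recorded by the biosensor and by an ActiGraph on the same wrist. The paragraph ends: "The results from the most successful trial will be utilized for subsequent analyses". It does not say what makes one test more successful than the other, and it does not separate functional outcomes from device agreement.

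Outcomes {12} lists as its first primary outcome "the concordance between HR and step count measurements assessed by the biosensor under test compared to standard devices".

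Statistical methods {20a} plans a paired comparison (t-test or Wilcoxon) of resting HR, maximum HR and step count, plus ICC and Bland-Altman analysis. It does not mention the second test. The same section lets the study move on from phase 1 if "the standard error between the biosensor under test and the reference measurements is within 5" per cent.

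Sample size {14} says "a convenience sample of 15 individuals without medical contraindications for PA will be studied", and "Assuming a sample loss of 30%, we will recruit 20 participants".

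**The concern.** Choosing the better of two walks is a usual way to handle a performance measure: the quantity of interest is the most a person can do, and a weaker attempt is a poorer measure of it. Agreement between two devices is a different quantity. Each walk gives a sensor value and a reference value for the same effort, and the pair is valid however far the person walked. Dropping one of the two walks therefore serves no purpose for agreement.

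The selection sentence nevertheless covers later analyses without distinction, and the section on statistical methods does not bring the other test back. An analyst who follows the text would estimate bias, limits of agreement and ICC from one session per person, in a small convenience sample, for a primary outcome on which the decision to leave phase 1 depends. The unused sessions have already been recorded.

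**Working it through.** **Inputs from the protocol article.** Two ISWTs per participant, one retained (Phase 1 section). Planned sample 15, with 20 recruited (Sample size {14}). The within-person correlation r between the sensor-reference differences in the two tests is not given, so I assume a range from 0 to 1. I also assume that the differences have the same SD in both tests.

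**The plan's own figure.** 15 × 1.3 = 19.5, rounded up to 20, which matches the stated recruitment. The 15 is a convenience sample, so there is no power formula to reproduce.

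**Sessions.** 15 × 2 = 30 recorded and 15 analysed, so half are unused. If all 20 recruits complete, the figures are 40 and 20. These are test sessions: HR is recorded continuously, and each session supplies resting HR, maximum HR and a step count.

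**Mean device difference.** With one test per person the variance of the mean is SD²/n. With two it is SD²(1 + r)/(2n). The ratio of standard errors is √((1 + r)/2), and the effective n is 2n/(1 + r).

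**Limits of agreement.** The approximate 95% CI half-width, in units of the SD of the differences, is t(n−1) × √(1/n + 1.96²/(2(n−1))) with one test. With two tests, 1/n becomes (1 + r)/(2n) and 1/(2(n−1)) becomes (1 + r²)/(4(n−1)). For n = 15, t(14) = 2.145, and one test gives 2.145 × √(0.0667 + 0.1372) = 0.97.

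| n = 15 | Effective n for the mean | SE ratio | SE reduction | Half-width, mean (SD) | Half-width, limit (SD) |
|---|---|---|---|---|---|
| One test | 15 | 1 | – | 0.55 | 0.97 |
| Both, r = 0 | 30 | 0.707 | 29% | 0.39 | 0.68 |
| Both, r = 0.5 | 20 | 0.866 | 13% | 0.48 | 0.79 |
| Both, r = 0.8 | 16.7 | 0.949 | 5% | 0.53 | 0.89 |
| Both, r = 1 | 15 | 1 | 0% | 0.55 | 0.97 |

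**Does the selection bias agreement?** I used a simulation of 400,000 participants with two tests each. Walking performance was standard normal and independent between tests, the better walk was kept, and the SD of the sensor error was exp(b × performance). The slope b is assumed. The table gives the SD of the error in the kept tests divided by that in all tests.

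| b | −0.5 | −0.3 | 0 | 0.3 | 0.5 |
|---|---|---|---|---|---|
| SD ratio | 0.69 | 0.82 | 1.00 | 1.15 | 1.23 |
| Dropped test has the larger error | 66% | 60% | 50% | 40% | 34% |

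Selection on walking performance can therefore understate sensor error, overstate it or leave it unchanged. Only if success were judged on sensor agreement itself would the result be flattering by construction (ratio about 0.60), and nothing in the article says that it is.

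**The case against.** The strongest reply is that the sentence was meant for functional capacity only. It closes a paragraph that lists distance, speed, VO2, blood pressure, exertion and stopping stage, and success is a natural word for a walking performance. The later use of the ISWT under Prescription of physical exercise is to set intensity. The description of the Bland-Altman and ICC analyses does not itself restrict them to one test. This reading is plausible and may be what the authors intend. But the sentence does not say so, the same paragraph includes the paired HR recording, and the section heading covers biosensor validation. The text needs one clarification either way.

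A reader might also infer that the rule tilts the result towards better agreement by leaving out the test in which the sensor did worse. The document does not support that. Nothing links success to sensor performance, and the direction of any effect depends on a relation between walking performance and sensor error that is not given. The progression criteria also say that substantial recording failures in earlier phases bear on the decision to proceed, without limiting this to the retained test.

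A reader might further infer that the phase 1 decision rests on only 15 pairs of readings. The correct count is about 15 sessions, or up to 20, each with several readings. Sensor checks also continue in later phases.

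Finally, the gain may be small. If a person's sensor error is nearly the same in both tests, the second test adds little. The model used for repeated tests is a detail that a condensed article may leave to a fuller document. The rule that selects the data, however, is stated here, and it is the rule that needs correcting.

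**Conclusion.** The point holds as one of wording and precision. As written, the rule sends one of two valid paired sessions per participant to no use in the analysis of a primary outcome. With 15 participants that is 15 of 30 sessions. The information lost is less than half unless the differences in the two tests are uncorrelated: the avoidable excess in the standard error of the mean difference corresponds to a reduction of 29%, 13%, 5% or 0% at r = 0, 0.5, 0.8 or 1. These figures rest on an assumed r and equal SDs, and on the literal reading of the selection sentence. No claim of bias in either direction can be made from the document. This is a worthwhile improvement and does not threaten the trial's validity.

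**What to change.** Three changes to the text:

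1. Limit the best-test rule to the functional capacity outcomes (distance, stage, VO2), and state what makes a test the more successful one.
2. For phase 1 HR and step agreement, use both ISWTs of every participant in a repeated-measures Bland-Altman and ICC analysis with participant as a random effect. Build the limits of agreement from the sum of the between- and within-participant variances of the differences. Do not average the two tests first, which would make the limits too narrow, and do not treat 30 sessions as independent.
3. Count missing or failed sensor recordings from both tests under the existing progression rule on recording failures.

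The cost is a slightly more complex analysis; no participants, visits or measurements are added. One consequence should be noted. If the standard error in the 5% rule means the standard error of the mean difference, using both tests makes that rule easier to meet. The change improves the estimate of agreement and does not make the progression rule stricter. If phase 1 is already complete, the analysis can be done on the retained recordings of the other test.
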